## Abstract

**Background:**

Cancer-related fatigue (CRF) is the most common side effect of cancer and cancer treatment. CRF prevalence is up to 50% in breast cancer patients and can continue several years after cancer remission. This persistent subjective sense of exhaustion is multifactorial. Numerous parameters have been evidenced to be related to CRF across biological, physical, psychological, social and/or behavioral dimensions. Although CRF has been studied for many years, the majority of previous studies focused on only one dimension, i.e., physical function. Moreover, few studies investigated CRF longitudinally with repeated measures. These are the two main obstacles that limit the understanding of CRF mechanisms. The purpose of this study is to create a biopsychosocial model of CRF with simultaneous and longitudinal anthropometric, clinical, biological, physical, psychological and sociological parameters.

**Methods:**

BIOCARE FActory is a multicentric prospective study that will consist of an 18-month follow-up of 200 women diagnosed with breast cancer. Four visits will be scheduled at diagnosis, after treatments, and 12 and 18 months after diagnosis. The same procedure will be followed for each visit. Each session will be composed of anthropometric data collection, a semi-structured interview, cognitive tests, postural control tests, neuromuscular fatigability tests and a cardiorespiratory fitness test. Clinical and biological data will be collected during medical follow-ups. Participants will also complete questionnaires to assess psychological aspects and quality of life and wear an actigraphy device. Using a structural equation modeling analysis (SEM), collected data will build a biopsychosocial model of CRF, including the physiological, biological, psychological, behavioral and social dimensions of CRF.

**Discussion:**

This study aims to highlight the dynamics of CRF and its correlates from diagnosis to post treatment. SEM analysis could examine some relations between potential mechanisms and CRF. Thus, the biopsychosocial model will contribute to a better understanding of CRF and its underlying mechanisms from diagnosis to the aftermaths of cancer and its treatments.

**Trial registration:**

This study is registered at ClinicalTrials.gov (NCT04391543), May 2020.

## Background

Cancer and cancer treatments induce various side-effects, the most reported being cancer-related fatigue (CRF). CRF is defined as ‘a distressing persistent subjective sense of physical, emotional, and/or cognitive tiredness or exhaustion related to cancer or cancer treatment that is not proportional to recent activity that interferes with usual functioning’ [1]. In breast cancer patients, CRF prevalence is up to 50% and can persist two years after cancer remission for 30% of patients and 5 years after for 20% [2]. CRF is extremely disturbing to quality of life and can decrease survival (overall and recurrence-free survival) [3]. Numerous parameters have been evidenced to be related to CRF among biological, physical, behavioral, psychological and/or social dimensions [4] (Table 1). Below is a summary of the main correlates of CRF (for extensive reviews see 5,6,7).

**Table 1 Tab1:** Hypothesized mechanisms of CRF and corresponding dimensions (adapted from McNeely and Courneya 2010)

Physiological	Biological	Psychological	Behavioral	Social
• Muscular strength • Muscular endurance • Cardiopulmonary fitness • Body composition	• Inflammatory response • Metabolic function • Endocrine function • Immune function	• Anxiety • Depression • Distress • Cognition	• Sleep quality and quantity • Appetite	• Social interactions • Positive reinforcement

Anthropometric data such as BMI or age have been, respectively, positively and negatively correlated to CRF severity [5–8]. Clinical data such as treatment type and disease stage have been associated with higher severity of CRF [9–11]. This relationship, however, remains unclear, and Bower et al., [12] concludes that treatment-related factors accounted for only a small portion of CRF.

Biological parameters extracted from blood samples, such as inflammation and anemia, have been related to CRF in breast cancer survivors through elevated levels of pro-inflammatory cytokines (e.g., TNF-α, IL-6) and reduced hemoglobin levels, respectively [13, 14].

Regarding physical parameters, CRF patients are more susceptible to sarcopenia, a substantial loss of skeletal muscle, thereby altering muscle strength and endurance [15]. This decrease in the force-generating capacity of the neuromuscular system during exercise, or neuromuscular fatigability, is higher in cancer patients suffering from CRF and is probably controlled by a specific central etiology [16–20]. Cardiorespiratory deconditioning is also linked to CRF; VO_2peak_ and power output at the lactate threshold have been correlated to CRF’s severity in cancer survivors [21], possibly due to the cardiac toxicity of some chemotherapies [22].

Behavioral parameters such as sleep disturbances are highly prevalent (up to 70%) in patients experiencing CRF [23]. Recent objective measures of sleep showed that onset latency, wake time at night, and sleep efficiency were correlated with CRF severity [24]. Lastly, duration and intensity of spontaneous daily physical activities are also related to CRF, as patients show an increase in leisure time and low intensity activities (< 2.5 metabolic equivalent task, METs) compared to those without CRF [25].

The relationship to psychological dimensions is also well established. Using specific questionnaires, anxiety and depression were investigated in breast cancer patients across many years and were strongly correlated with CRF severity [26]. Coping strategies, particularly catastrophizing (a lack of confidence and an expectation of negative outcomes), may be associated with CRF [27]. Furthermore, women with breast cancer may undergo surgical mastectomy in addition to chemotherapy, which impacts body image, self-esteem and may lead to depressive symptoms [28, 29]. Cognitive processes, such as attention, concentration and memory, are affected before and during treatments and related to CRF [30]. These cancer-related cognitive impairments have been frequently attributed to chemotherapy neurotoxicity and dubbed “chemo fog” or “chemobrain” [31]. As part of the social dimension of CRF, social networks and support were studied using questionnaires and interviews. Generally, the lack of social support was identified as a factor of fatigue in chronic fatigue syndrome [32]. Among breast cancer patients, those who reported lower levels of social support had elevated CRF [33].

Despite the numerous studies investigating CRF correlates, including their potential mechanisms and the well-known multidimensional nature of CRF, the majority of previous studies have remained mainly focused on a specific dimension (e.g., biological or psychological). This is a significant limitation to understanding the relationships between all of the known correlates of CRF. There are, however, a few studies that have combined some of the above-mentioned dimensions in order to investigate CRF mechanisms. For example, Stone et al., [34] designed a model using a multiple linear regression, explaining 56% of CRF variance including anxiety-depression, dyspnea and pain, and a disease burden score. More recently, Lockefeer et al., [26] used depressive symptoms, sleep quality and CRF before diagnosis (or primary surgical treatment) in breast cancer patients to predict CRF at 24 months. Only CRF before diagnosis was a significant predictor of CRF two years later and explained 33% of CRF variance. Humpel et al., [35] also investigated the relationship between sleep disturbances, CRF and physical activity in patients with breast cancer. Their CRF prediction model included sleep quality and total physical activity and resulted in a 46% CRF variance prediction. Nevertheless, they focused exclusively on the behavioral dimensions of CRF. Recently, CRF prediction has been studied by combining neuromuscular, emotional and behavioral dimensions [20]. The results evidenced that a model including anxiety-depression, sleep disturbances and neuromuscular fatigability explained 56% of CRF variance. CRF variances described by the above-mentioned studies ranged from 33 to 56%, leaving unexplained variations which could be related to dimensions not yet considered.

Most studies investigating CRF were cross-sectional and thus cannot account for the dynamics of these mechanisms, and few studies implemented longitudinal follow-ups. Some longitudinal studies have focused on the psychological dimension and their results are unanimous in asserting that anxiety before treatment was a strong predictor of subsequent CRF in breast cancer patients [26, 36, 37]. At best, these various studies combine only two different dimensions (behavioral and psychological, biological and psychological, clinical and psychological, respectively). Only Bower et al., [5] have led a longitudinal study in breast cancer patients that combines more than two dimensions of CRF, from diagnosis to 18 months post treatment. They have investigated biological, demographic, social, clinical and psychological dimensions. Unfortunately, only baseline results are currently available. They reveal that younger age, lower educational level, lower disease stage and history of childhood maltreatment were found to be significant predictors of CRF.

Recent studies have highlighted the necessity to develop longitudinal and multidimensional researches in order to identify potential mechanisms explaining CRF [8, 38]. Therefore, the purpose of this longitudinal study is to build a biopsychosocial model of CRF by simultaneously investigating anthropometric, clinical, biological, physical, psychological and sociological parameters using structural equation modeling (SEM).

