### Anthropometric data

Body height, body mass, lower limb fat mass (using impedancemetry) and calf circumference (CC) will be measured. CC will be recorded to assess the dominant lower limb volume using the truncated cones technique [39] by dividing the lower limb volume into a series of segments. Then, the lower limb volume will be used to normalize maximal strength of participants. CC under 31 cm will serve as a clinical indicator of sarcopenia [40].

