### Semi-structured interview

To investigate the social dimension of CRF, a semi-structured interview will be conducted (duration ~ 30 min). Demographic (e.g., age, gender, socio-professional category, residence area, income) and sociability (e.g., family, friendly, professional) will be addressed. The interview will be introduced by an open question on a typical week to then develop the sociability. The entire interview will be audio recorded, fully transcribed and then will be the subject of a lexicographical treatment for rating quantity and intensity of sociability (on a scale from − 5 to 5). In order to build a typology of patients’ sociability, researchers will also assess the level of social ties’ perception. Lastly, family, friendships, professional sociabilities and income will be considered in the SEM analysis.

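### Age and BMI are named as correlates of fatigue and are collected or derivable, but neither enters the SEM, so between-person paths to CRF are left open to confounding, chiefly by age

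*Protocol article*

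**What the plan says.** The Background of the protocol article reports that "Anthropometric data such as BMI or age have been, respectively, positively and negatively correlated to CRF severity". It later describes another longitudinal study in breast cancer, in which "younger age, lower educational level, lower disease stage" were among the baseline predictors of CRF. It then sets the purpose of the present study: to build a model of CRF "by simultaneously investigating anthropometric, clinical, biological, physical, psychological and sociological parameters using structural equation modeling (SEM").

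The measurements exist. Under Anthropometric data, "Body height, body mass, lower limb fat mass (using impedancemetry) and calf circumference (CC) will be measured", so BMI can be derived although it is not itself listed. Under Semi-structured interview, age is among the demographic items: "Demographic (e.g., age, gender, socio-professional category, residence area, income").

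None of these variables except income reaches the model. The interview section sends only the three sociability ratings and income to the SEM. The anthropometric section sends nothing. Its stated uses are that "the lower limb volume will be used to normalize maximal strength of participants" and that calf circumference serves as a clinical sign of sarcopenia. Table 3 lists 28 manifest variables under 6 latent variables, without age, BMI, height, mass, fat mass or calf circumference. The Sample size section counts 6 predictors and equates them with the 6 latent variables.

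**The concern.** Two things are at stake.

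- **The purpose and the specified model disagree.** Anthropometric parameters are announced as part of the SEM and are absent from the table that defines it.
- **A named correlate of the outcome is left out.** Table 2 admits women from 18 to 80. Several Table 3 indicators plausibly vary with age: power at the first lactate threshold (entered in absolute watts), TMT time, Stroop interference, MoCA, sway area, CT sarcopenia and professional sociability. If age is related both to these and to CRF, part of any estimated path from those constructs to CRF reflects age.

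The Statistical analysis section adds weight to this, because non-significant paths are to be deleted. A path weakened by an omitted covariate may drop out of the final model, and a path created by one may stay in.

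**Working it through.** **1. The plan's own figure.** Inputs from the Sample size section: n = 200, power 0.90, α = 0.05, 6 predictors, F test for R² increase. With noncentrality λ = f²·n, df1 = 6 and df2 = 200 − 6 − 1 = 193, solving for power 0.90 gives f² = 0.0900. The stated 0.09 is reproduced.

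**2. Cost of two covariates by the same method.** Testing 6 of 8 predictors gives df2 = 191.

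| n | f², 6 of 6 | f², 6 of 8 |
|---|---|---|
| 200 | 0.0900 | 0.0900 |
| 160 | 0.1134 | 0.1135 |

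Here 160 = 200 × 0.80, which reads the 20% drop-out as a loss from the 200. Adjustment costs essentially no power.

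**3. Age-only illustration.** The documents give no coefficients, so these standardised values are assumptions: true Physical-to-CRF path b = -0.25; age-to-CRF g = -0.20 to -0.25 (only the sign comes from the Background); age–Physical correlation r = -0.4 to -0.5.

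Path estimated when age is omitted, b + g·r:
- -0.25 + (-0.20)(-0.4) = -0.17
- -0.25 + (-0.25)(-0.5) = -0.125

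Age–CRF correlation, g + b·r:
- -0.20 + (-0.25)(-0.4) = -0.10
- -0.25 + (-0.25)(-0.5) = -0.125

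Partial correlation of Physical with CRF when age is included:
- [-0.17 − (-0.4)(-0.10)] / √[(1 − 0.16)(1 − 0.01)] = -0.21 / 0.912 = -0.230
- [-0.125 − (-0.5)(-0.125)] / √[(1 − 0.25)(1 − 0.0156)] = -0.1875 / 0.859 = -0.218

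Power of the single-path F test, two-sided 5%, N = 160:

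| Assumed g, r | Age included | Age omitted |
|---|---|---|
| -0.20, -0.4 | about 84% | about 58% |
| -0.25, -0.5 | about 80% | about 35% |

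**4. The converse case.** If the true path is zero, omission creates a spurious path of size |r|·|g|. With assumed values and n = 200, the chance that a nominal 5% test (Fisher z) calls it significant is:

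| Assumed \|r\|, \|g\| | Spurious path | Rejection rate |
|---|---|---|
| 0.2, 0.1 | 0.02 | about 6% |
| 0.3, 0.2 | 0.06 | about 13.5% |
| 0.4, 0.2 | 0.08 | about 20% |
| 0.5, 0.3 | 0.15 | about 56% |

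**5. Adding BMI.** Suppose BMI is independent of age, with effect +0.20 on CRF and correlation -0.4 with Physical (assumed). Omitting both then gives -0.25 + 0.08 + (0.20)(-0.4) = -0.25, so the two biases cancel. The net direction therefore cannot be fixed from the documents.

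**The case against.** **A condensed article may leave covariates to the full protocol or analysis plan.** Table 3 is headed as latent and manifest variables, so an observed covariate might be specified elsewhere. This limits any claim that no adjustment is planned. It does not remove the mismatch: the article states what enters the SEM measure by measure, lists age as collected and then admits other interview items, and promises anthropometric parameters that its own table lacks.

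**A reader might infer that the paths are confounded, and that age drives CRF.** The documents do not support either. They report a correlation, and a prediction from another study's baseline results. They give no link from age or BMI to the physical, cognitive or social constructs. Those links are plausible across ages 18 to 80, but they are an assumption. That the paths are left open to confounding is as far as the text goes.

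**A reader might infer that the omission costs a third to a half of the effect.** That describes the age-only, single-predictor illustration. An equal BMI effect could cancel it, and the other latent variables in the model could absorb part of it. Nor would adjustment restore the power of a partial correlation of 0.25: because age and Physical are correlated, the partial correlation is 0.23 to 0.22.

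**Scope.** Age is close to a between-person constant over 18 months, so it hardly touches within-person paths. This stands and narrows the point. The by-visit analyses and the between-person level remain affected, and the latter is the level at which the plan judges its power.

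**BMI.** It may be partly a mediator. Some body-size dependence is already reduced: the force asymptote is a percentage of the woman's own maximum, voluntary activation and the evoked doublet are scaled to her own pre-test values, and the lumbar muscle index is normalised to stature. This stands for BMI, but none of it adjusts for age.

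**Conclusion.** The omission and the contradiction with the stated purpose are established from the text. The consequence is a risk of confounding, mainly by age, in the by-visit cross-sectional paths and the between-person paths from the physical, cognitive and social constructs to CRF. Its size and net direction are not established. The fall in power from about 84–80% to about 58–35% at N = 160 rests wholly on assumed values for age alone and one predictor. The case is clear for age and weaker for BMI. The change is worth making because the data are already collected, the adjustment is nearly free, and significance decides which paths survive.

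**What to change.** - Add age as an observed exogenous covariate, with paths to CRF and to the other latent constructs, in each by-visit model and at the between-person level of the longitudinal model.
- Add baseline BMI, derived from height and body mass, in the same way with its role stated. Alternatively, report it as a sensitivity analysis, because it may be partly a mediator.
- Align Table 3 with the purpose in the Background. If either variable is to stay out, give the reason and amend the purpose.

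The cost is a few structural parameters: paths to CRF and to the five other latents make six per covariate. No new data are needed. By the plan's own power method, the detectable f² stays at about 0.09 at n = 200.

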## Methods/design

### Study population

Two hundred women newly diagnosed with breast cancer by an oncologist and satisfying inclusion and exclusion criteria (Table 2) will be informed of the study protocol. If interested, patients will receive an information letter from their oncologist and will be given the opportunity to ask any questions pertaining to it. After a 48 h period of reflection, study coordinators will phone the patients to confirm their participation, obtain a written consent form and schedule their first visit.

**Table 2 Tab2:** Inclusion and exclusion criteria

Inclusion criteria	• Patients care by chemotherapy or radiotherapy in Clinique Victor Hugo-Centre Jean Bernard, Le Mans, France or in Centre Hospitalier du Mans, Le Mans, France
	• Patients with breast cancer diagnosis (Stage I to IIIc)
	• Aged ≥18 and ≤ 80 years
	• Approval received from oncologist
	• ECOG Performance Status ≤2
	• French speaking (able to understand questionnaires and instructions related to study procedures)
	• Written informed consent obtained
**Exclusion criteria**	• Comorbidities related to fatigue symptoms
	• Polyneuropathy, amyotrophy or myasthenic syndrome diagnosis
	• Contraindications to physical activity or to experimental procedures
	• Antidepressants, psychostimulants, psychotropics, antiépileptics or benzodiazepine based treatment
	• Previous or current psychosis, bipolarity or severe depression symptoms
	• History of chronic fatigue, stroke or musculoskeletal disorders
	• Participant is pregnant

### Study design

This prospective multicentric (Clinique Victor Hugo-Centre Jean Bernard, Le Mans, France and Centre Hospitalier du Mans, Le Mans, France) study will consist of an 18 month follow-up of a women cohort with breast cancer. Four visits will be scheduled (the study timeline is presented in Fig. 1). Detailed patient assessments will be performed before treatment begins (visit 1: diagnosis); during the week after completion of the first-line treatment, or 6 months after diagnosis, whichever comes first (visit 2); and then 12 and 18 months after diagnosis (visit 3 and 4, respectively). This study has been approved by the French ethics committee of human research CPP SUD EST VI (IDRCB: 2019-A02525–52) and will be performed according to the Declaration of Helsinki. Furthermore, this study protocol has been written in accordance with the SPIRIT guidelines (SPIRIT Checklist provided in Additional file 1) and is registered in a database (ClinicalTrials.gov, NCT04391543, May 2020). In order to longitudinally assess the evolution of biopsychosocial dimensions of CRF, the same procedure will be followed for each visit. Each session will last 1.5 h and will be composed of anthropometric data collection, a semi-structured interview, cognitive tests, postural control tests, neuromuscular fatigability tests and a cardiorespiratory fitness test. Clinical and biological data will be collected during medical follow-ups. In addition, participants will be asked to wear an actigraphy device (received by mail one week prior to each experimental session) and to complete questionnaires to assess psychological aspects and quality of life.

**Fig. 1 Fig1:**
[figure not shown]
Flowchart of the study design

### Anthropometric data

Body height, body mass, lower limb fat mass (using impedancemetry) and calf circumference (CC) will be measured. CC will be recorded to assess the dominant lower limb volume using the truncated cones technique [39] by dividing the lower limb volume into a series of segments. Then, the lower limb volume will be used to normalize maximal strength of participants. CC under 31 cm will serve as a clinical indicator of sarcopenia [40].

### Semi-structured interview

To investigate the social dimension of CRF, a semi-structured interview will be conducted (duration ~ 30 min). Demographic (e.g., age, gender, socio-professional category, residence area, income) and sociability (e.g., family, friendly, professional) will be addressed. The interview will be introduced by an open question on a typical week to then develop the sociability. The entire interview will be audio recorded, fully transcribed and then will be the subject of a lexicographical treatment for rating quantity and intensity of sociability (on a scale from − 5 to 5). In order to build a typology of patients’ sociability, researchers will also assess the level of social ties’ perception. Lastly, family, friendships, professional sociabilities and income will be considered in the SEM analysis.

